## Abstract

**Background:**

Stroke remains a leading cause of disability globally, creating significant challenges for healthcare systems. Early intensive rehabilitation is recommended (NICE2023) for functional recovery; but standard therapy may not cover all patients’ needs. Stroke survivors should continue active task practice outside of scheduled therapy sessions (self-directed, or semi-supervised by family and caregivers), possibly by sustainable technological solutions. However, most technology-based ecosystems are not designed for healthcare. To test a digital stroke rehab ecosystem Randomized Clinical Trials (RCTs) are the gold standard, but present ethical and logistical challenges, particularly in blinding and participant adherence. This study protocol (ClinicalTrials.gov; NCT06728020; March 21 st, 2025) employs a cohort multiple RCT (cmRCT) innovative design, suitable for comparing usual care to interventions in studies with multiple interventions: cmRCT enrols a large observational cohort, allowing random selection of participants for individual trials rather than random allocation for all subjects, alongside a patient-centered approach to information and consent.

**Methods:**

A certified device including a multimedia monitor with virtual reality cognitive and motor rehabilitation exercises (VRRS) will be enriched with educational videos and rehabilitation contents, developed by co-creation involving stroke patients, caregivers and rehabilitation professionals (VRRS1). A dynamic cohort of post-acute stroke inpatients will then be prospectively enrolled in a cmRCT: first, the VRRS1 will be randomly proposed to and tested with 70 subjects, while 70 other eligible patients will be randomized to Usual Care (UC) - controls (ROOMMATE 1st); then, the VRRS1, integrated with a set of inertial sensors (BMR4ROOMMATE) (VRRS2), will be tested in a pilot RCT on 30 patients (while 30 other eligible patients will be randomized as controls - ROOMMATE 2nd). The primary outcome will be the Modified Barthel Index, while secondary outcomes will include measures of motor and cognitive functions, as well as feasibility, usability, and device wearability.

**Conclusion:**

By combining sensor-based assessment, expert coaching on digital literacy, and the active involvement of patients, caregivers, and healthcare professionals ROOMMATE aims to co-create an innovative digital ecosystem for Stroke rehabilitation. By rigorously verifying its impact by a cmRCT, it seeks evidence to enhance stroke recovery beyond usual care.

## Introduction

1

Neurological disorders are a leading cause of disability worldwide, stroke being the most prevalent. In 2017, there were 1.12 million incident strokes in the European Union and 9.53 million stroke survivors. Also, stroke prevalence is estimated to increase by 27% between 2017 and 2047, due to population aging and to improved survival rates (1), and stroke-related disability is estimated to have a parallel increase (2).

Early intensive rehabilitation and an enriched environment are important promoters of neuroplasticity and functional recovery after stroke. However, even after intensive rehabilitation, stroke survivors often achieve limited recovery in cognitive and motor functions, activities and participation (2). Stroke patients’ associations report (3) that patients feel abandoned, with unmet needs including disease-related information, physical recovery and activity/participation, social environmental resources, and psycho-emotional support. Indeed, in typical hospital settings patients lack structured planned activities for long hours outside of scheduled rehabilitation activities, and frequently due to economic and organizational constraints (3) they also tend to be disengaged and isolated from their families for most of the day.

Recent updates from the 2023 NICE stroke guidelines further emphasize that people after stroke should be offered needs-based rehabilitation for at least 3 h per day, on at least 5 days per week, delivered through a multidisciplinary approach including physiotherapy, occupational therapy, and speech and language therapy (4, 5), but also highlights the importance of encouraging stroke survivors to continue active task practice outside of scheduled therapy sessions, through self-directed or semi-supervised practice, and with the involvement of family and caregivers whenever appropriate (5).

Technology provides opportunities to optimize rehabilitation services by providing sustainable, intensive interventions addressing more functioning domains at once, but its impact on rehabilitation outcome and the cost-effectiveness of technology-based rehabilitation interventions on stroke patients require further evidence (4, 6). Further, the acceptance of rehabilitation technologies is mainly hindered by the limited health and digital literacy of potential users. Almost 50% of European citizens have low levels of health literacy, and even lower levels of digital literacy, and structured coaching programs to support different end users towards adoption of technological components are lacking (7). Finally, most of the digital health ecosystems have been developed over existing platforms, created and implemented for purposes not specifically directed to care and services provision; these ecosystems generally do not take into account standards required for medical technologies (8) nor the lack of skills of real users (9).

Previous studies highlight that co-creation in stroke rehabilitation is still in a rudimentary phase, with inconsistent terminology and diverse methodologies (10, 11). Also, digital therapies have shown promise in improving clinical outcomes, patient empowerment and quality of life; however, challenges remain in extending benefits to those with severe neurological impairments and in addressing digital health equity (12). While numerous subsystems, such as telehealth, exergaming, virtual reality, robotics, mobile health apps and digital support platforms have been developed, very few examples of health technology ecosystems exist (13), where these components integrate to support multiple clinical processes, shifting toward, patient-centered care, with key implications for rehabilitation quality and resource allocation in digital health. Indeed, the assessment of these systems should consider several domains, i.e., feasibility, usability, acceptability, user’s experience, effectiveness and cost–benefit ratio. Regarding the last two, a relevant issue is to identify a study design that allows the pragmatic investigation of the different components of the ecosystem. The NICE 2023 guidelines further acknowledge that telehealth services may be used either as an adjunct or as an alternative to in-person therapy, particularly for patients unable to access community rehabilitation. Importantly, delivering interventions via telehealth should be restricted to approaches with proven benefits (5, 14). This provides strong support for testing bedside telerehabilitation within neurorehabilitation units as part of structured, needs-based care.

In clinical research, the Randomized Controlled Trial (RCT) study design is considered the gold standard approach to verify the effectiveness of an intervention (15). On the other hand, the feasibility of RCTs in physical and rehabilitation medicine raises ethical as well as practical issues. Since RCTs require full disclosure of the protocol, problems with this study design also concern patient preferences, which can be a major issue for adherence, particularly when participants are not blind to group allocation. Patients may be less motivated to participate if they suspect or know for sure that they will not receive the experimental treatment. This may lead to refusal to participate, withdrawal or less compliance with the protocol. The cohort multiple RCT (cmRCT) is an innovative design that attempts to overcome these issues related to traditional RCT (16). The key features of this design are: (I) recruitment of a large observational cohort of patients with the condition of interest, providing consent to the observational study and to be eventually enrolled in multiple RCTs; (II) regular measurement of outcomes for the whole cohort (III); capacity for multiple randomized controlled trials over time. For each randomized controlled trial, (IV) identification of all eligible patients in the whole cohort (NA); (V) random selection of some patients (nA) from all eligible patients in the cohort, who are then offered the trial intervention; (VI) comparison of the outcomes in randomly selected patients (B) with the outcomes in eligible patients not randomly selected; that is, those receiving usual care (UC) (NA − B); (VII) “Patient centred” informed consent to the experimental intervention; that is, the process of obtaining patient information and consent aims to replicate that in real world routine health care, when you actually will provide the intervention you propose if the participant accepts. The cohort multiple RCT allows the simultaneous evaluation of the effectiveness of several interventions (16). In cmRCTs, ethical requirements are not violated due to the fact that all cohort subjects are informed about the study design at the time of enrolment in the study cohort, when they are asked for informed consent to participate and also agree to be either contacted for receiving experimental interventions or to serve as controls without additional notification (16).

In this context, the ROOMMATE project, co-funded by the European Union within the “Transforming Health Care Systems” call (GA N° 101,095,654 of the Horizon Europe Research and Innovation Program), seeks to address these challenges, by involving all stakeholders (patients, caregivers, health professionals) in the co-creation of a technology supported ecosystem to optimize stroke rehabilitation, and testing it against usual care (UC).

Our hypothesis is that the implementation of such ecosystem will be feasible, usable and appreciated by users. We also hypothesize that it will improve functional recovery in stroke survivors undergoing post-acute intensive rehabilitation, compared to usual care (UC).

## Materials and methods

2

### Study design

2.1

The registration on ClinicalTrials.gov has been completed and the study has been reviewed obtaining the identification number “NCT06728020.” This study was prospectively registered as an international multicenter no-profit cmRCT and developed according to the Standard Protocol Items: Recommendations for Interventional Trials (SPIRIT) checklist (17), as detailed is in Supplementary material.

First, we will develop educational videos and rehabilitation contents, co-created with patients, caregivers and rehabilitation professionals, and introduce them into a certified device a multimedia system that already includes virtual reality cognitive and motor rehabilitation exercises (VRRS1). VRRS1 will be tested in a first RCT (ROOMMATE 1st), providing expert coaching on its use throughout the intervention. Subsequently, VRRS1 will be integrated with a set of inertial sensors (BMR4ROOMMATE) and this integrated system (VRRS2) will be tested in a second pilot RCT (ROOMMATE 2nd).

### Study setting

2.2

The study will be conducted at the Don Carlo Gnocchi Foundation (FDG) in Florence and the Elias University Emergency Hospital (EUEH) in Bucharest. FDG is the coordinator clinical center, with dedicated facilities and multidisciplinary expertise in post-stroke rehabilitation and innovative digital rehabilitation approaches. EUEH is one of Romania’s major university hospitals, hosting specialized units for acute and post-acute stroke care, and expertise in health technologies co-creation.

### Participants

2.3

Two hundred persons with stroke outcomes admitted to the neurorehabilitation wards of (100 participants each) will be enrolled in the study cohort. All consecutive patients meeting the eligibility criteria will be included until the prospected sample size is reached. Both clinical sites applied the same eligibility criteria to ensure consistency in patient selection. The enrollment was competitive.

Inclusion criteria:

age ≥ 18 years;outcome of ischaemic or haemorrhagic stroke in subacute phase (< 3 months from the event);the ability to use devices included in the digital ecosystem independently or in the presence of a caregiver who can assist the patient in using the system;willingness to participate in the project, with informed consent signed by the patient or by his/her immediate relatives/legal guardians, when necessary.Exclusion criteria:severe uncorrectable visual and/or hearing impairment;Skin or other peripheral lesions that prevent the inertial sensors from being worn;Clinical signs of medical instability, defined by a score greater than zero on the Clinical Instability Score (CIS) (18).

### Devices description

2.4

The digital ecosystem will consist of a multimedia monitor apparatus, named Virtual Reality Rehabilitation System (VRRS). In particular, VRRS Home Kit Cognitive produced by Khymeia Group. VRRS is a CE-certified device for remote cognitive and speech therapy, supporting online therapist-led sessions and offline patient-guided exercises with real-time feedback. The system is tablet-based and provides modules for motor, cognitive, and language rehabilitation. It offers virtual rehabilitation, task-based feedback, automated performance tracking, and session reports, and enables the design of a personalized treatment plan that can be shared with the patient, and it is characterized by a user-friendly interface along with the ability to select different levels of difficulty when performing exercises. Within the ROOMMATE project, the device will be integrated with original educational and rehabilitation contents, co-created within the project’s framework, providing a bedside rehabilitation station (Figure 1) The device is classified as a Class I non-invasive medical device (MDR 2017/745).

**Figure 1 fig1:**
[figure not shown]
VRRS home kit cognitive.

The BMR4ROOMMATE system is classified as a Class I non-invasive medical device (MDR 2017/745) specifically designed for quantitative motion analysis in neurological and orthopedic research. Developed by the University of Florence, Department of Industrial Engineering (DIEF) within the Assistive BioRobotics Joint Lab, it combines wearable inertial sensors and a depth camera to provide detailed biomechanical assessments. BMR4ROOMMATE includes two sensorized rings and a wrist bracelet that together measure upper limb motion, capturing acceleration, angular velocity, and magnetic field data. Each unit integrates a 9-axis inertial sensor (accelerometer, gyroscope, and magnetometer) alongside an ARM Cortex-M3 microcontroller. Data from the rings and bracelet are synchronized via CAN-BUS protocol and transmitted to a PC through Bluetooth (Rigado BMD-350). The system acquires data at 100 Hz, ensuring high-resolution analysis. To accommodate different hand sizes, five interchangeable ring sizes are available (XS to XL). For the lower limb, the SensFoot module—housing the same sensor and processor—is anchored to the patient’s shoe, enabling gait and postural assessments without restricting foot movement. An Intel RealSense RGB-D camera complements the wearable sensors by providing three-dimensional depth data on patient movements, enhancing the overall biomechanical evaluation. The camera operates locally with no remote data exchange. The BMR4ROOMMATE device does not interfere with patient performance and is easy to wear, requiring only a standardized fitting procedure. The system is provided free of charge to participating clinical centers (Figure 2).

**Figure 2 fig2:**
[figure not shown]
BMR4ROOMMATE wearable device. It is composed of 3 inertial measurement units (IMUs) one placed on the wrist and two placed on the fingers.

### Procedure

2.5

The study will be carried out in the neurorehabilitation wards of the two clinical centers, involving inpatients undergoing subacute stroke rehabilitation. In detail, in line with the innovative vision of the project, the VRRS Home Kit Cognitive system, including the co-created educational and rehabilitation contents, will be available to patients and caregivers directly in their rooms. In particular, the device will be mounted at the patient’s bedside with an extendable arm, allowing the screen to be positioned in the most comfortable orientation for each patient, as shown in Figure 1. The BMR4ROOMMATE devices, on the other hand, will be used by the project’ research team, to provide a sensorized motor assessment of upper limb at different time points point during the rehabilitation and correlate it with the data on the patient’s motor performance in the VRRS upper limb exergames. The phases of the study are shown in Figure 3.

**Figure 3 fig3:**
[figure not shown]
Phases of the clinical protocol.

Phase 1: before starting to enroll participants, a preliminary phase (phase 1 of the ROOMMATE project) is planned to co-create the digital ecosystem and train end-users in its use. First, questionnaires will be administered, and semi-structured interviews, focus groups and workshops will be conducted with all the relevant stakeholders (rehabilitation healthcare professionals, persons with post-stroke disabilities, caregivers), according to a standardized co-creation methodology. Iterative feedback from these participative activities will be used to develop and test the educational and rehabilitation contents and tailor them to opinions, needs, preferences and values in regards to rehabilitation of relevant stakeholders (19, 20). Afterwards, all different categories of stakeholders will test the proposed technologies, in different stages of development of the solution, from wireframes to functional prototypes, and will be asked their feedback on their acceptability and usability in Living Labs (LLs), where they will be trained in the use of the system by e-health coaches (e-HC), chosen among the bedside researchers (physiotherapists, occupational therapists, speech therapists, psychologists, nurses) of the clinical sites, and trained for this task by a two-week course with a final examination on e-health and digital technologies mastership and on coaching skills. The focus groups will follow a standardized co-creation methodology (21), with structured discussions aimed at gathering insights from patients, caregivers, and professionals about unmet needs after a stroke, in order to shape the content of the digital ecosystem. During these meetings, however, VRRS devices will not be experienced by participants. Instead, in the living labs, participants will interact with VRRS1 to assess its usability and functionalities. The VRRS2, which incorporates the BMR4ROOMMATE inertial sensor for evaluation purposes, will not be included in these sessions. Phase 1 ensures that the digital ecosystem is shaped by real user needs before further testing. The qualitative results of the usability testing will be used to refine the user-technology interfaces and to create appropriate workflows to improve user experience and rehabilitation outcomes. The LL activities will be organized in the occupational therapy (OT) labs at both clinical sites, where techniques such as thinking aloud and discussions on specific aspects will be used, while the research team members offer cognitive walkthroughs and participants explore the workflows provided by the technologies on their own. Time and the success rate of participants while exploring and solving tasks using the technologies will be recorded to provide technology developers with valuable feedback in order to adapt the interfaces and the navigation to improve usability for the target populations.

In Phase 2 and Phase 3, the digital system developed in phase 1 will be tested and compared to UC. Two slightly different technologies assemblies, named VRRS1 and VRRS2, both aimed at building a technology supported enriched environment, will be studied in succession. VRRS1 includes all the motor, cognitive and speech therapeutic modalities embedded in the original VRRS plus the informative and rehabilitation contents co-created in the first phase of the project; VRRS 2 includes all the features of VRRS1, that will be integrated to the BMR4ROOMMATE devices, providing a specifically developed sensorized motor assessment of the upper limb.

In phase 2, the VRRS1 will be tested in a randomized controlled trial enrolling a dynamic cohort of 140 participants, by a competitive recruitment in the two Clinical Centres (FDG in Florence, EUEH in Bucharest) through the systematic assessment for eligibility of all patients addressed to either centre for post-stroke inpatient rehabilitation. Eligible patients who will sign the informed consent will be consecutively recruited in either centre. Half of them will be randomly assigned to be proposed to receive the intervention VRRS1 in addition to usual care, and to be enrolled after signing another informed consent, while the other 70 will serve as controls, receiving only usual care. This first RCT is called ROOMMATE 1rst. In parallel to phase 2, the technical partners will carry out the integration of the VRRS with the MB4ROOMMATE inertial sensor.

At the end of phase 2, in both Clinical Centres the cmRCT recruitment will continue as before to enroll a dynamic cohort of at least 60 subjects in total; half of them will be randomly extracted to be proposed to participate in a pilot RCT (ROOMMATE 2nd) to study the effects of the integrated system VRRS2 (phase 3), and enrolled if providing informed consent, while the other 30 will serve as controls receiving usual care.

The VRRS system includes the proprietary content developed by Khymeia, consisting in a structured set of motor and cognitive exercises, each targeting specific rehabilitation objectives:

Motor Deficit exercises: these exercises address impairments in movement and coordination and are designed to improve strength, range of motion and coordination; examples include arm elevation, reaching and grasping activities, trunk flexion-extension, ankle dorsal and plantar flexion;Cognitive Deficit exercises: these focus on visuospatial abilities, attention, and executive functions, using interactive tasks that require target tracking, hand-eye coordination, and memory recall.

Additionally, alongside this content, the VRRS1 system will incorporate rehabilitation and educational content co-created during Phase 1 of the project with key stakeholders, including patients, caregivers, and healthcare professionals. The exercises provided by the VRRS1 and later by the VRRS2 system will be chosen and performed according to the personalized prescription of the therapists taking care of the patient during his/her stay.

VRRS1 (and later VRRS2) will be tested as a bedside rehabilitation station and made available to patients, caregivers and rehabilitation professionals (physiotherapists, speech and language therapists, occupational therapists). Strategies to improve adherence to intervention protocols, and procedures for monitoring adherence, included the availability of an e-HealthCoach (e-HC) to support patients, caregivers, and therapists, fostering innovation adoption and promptly addressing any system malfunctions. Criteria for discontinuing or modifying allocated interventions included withdrawal of informed consent, clinical worsening, or any adverse effects attributable to the intervention. In the trial, no treatments deviating from usual care (UC), as described in the “Control intervention” paragraph, e.g., Functional Electrical Stimulation, neuromodulation, or other approaches will be permitted.

The randomization sequence will be generated using simple computer-generated randomization, while allocation concealment will be ensured through sequentially numbered, opaque, sealed envelopes, prepared by independent staff and opened in order at the time of enrollment. Smooth enrollment will be ensured through early patient identification, transparent information and privacy procedures, sustained engagement of clinical staff, and recruitment across multiple sites.

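### Simple randomisation does not secure the stated 70/70 and 30/30 arms and leaves balance between the two centres to chance

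*Protocol article*

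**What the plan says.** Section 2.5 (Procedure) names the method: "The randomization sequence will be generated using simple computer-generated randomization". Allocation is concealed by "sequentially numbered, opaque, sealed envelopes, prepared by independent staff and opened in order at the time of enrollment". The section mentions no blocking, stratification or minimisation, and does not say whether there is one envelope series or one per centre.

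The same section gives the arm sizes as exact. ROOMMATE 1st is described as "enrolling a dynamic cohort of 140 participants, by a competitive recruitment in the two Clinical Centres". Of these, "Half of them will be randomly assigned to be proposed to receive the intervention VRRS1 in addition to usual care", "while the other 70 will serve as controls, receiving only usual care". For ROOMMATE 2nd it plans a cohort of at least 60, with half drawn at random for the offer of VRRS2 and the other 30 as controls.

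On site shares, section 2.3 (Participants) has "100 participants each) will be enrolled in the study cohort" and, in the same paragraph, "The enrollment was competitive".

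Section 2.9 names a 2 × 2 repeated-measures ANOVA or, depending on the distribution, Mann-Whitney and Wilcoxon tests. No centre term is named.

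**The concern.** Simple randomisation treats each patient as an independent coin toss. It fixes neither the arm totals nor the arm totals within a centre, so the method and the exact halves in section 2.5 do not fit together as written.

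The centres are a rehabilitation foundation in Italy and a university emergency hospital in Romania. A difference between them in mBI change is plausible, although the article gives no figure for it. If one exists, any chance imbalance in centre between the arms moves the unadjusted contrast, and the named tests do not remove the centre component of variance. The article also gives two incompatible rules for how many patients each centre contributes.

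**Working it through.** **Inputs.** Totals of 140 and 60 and their halves (section 2.5); effect size 0.5, power 0.80, alpha 0.05, 64 per group raised to 70 for 10% drop-out (section 2.9). Assumed: two-sided testing, 1:1 allocation, and equal recruitment by centre (70 + 70, then 30 + 30) unless stated otherwise.

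**The plan's own figure.** The normal approximation, n = 2(1.96 + 0.84)²/0.5², gives 63 per group. The two-sample t-test gives 63.8, so 64, as stated. Inflating for 10% loss gives 64/0.9 = 71.1, so 72; the stated 70 is close and is not at issue here.

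**Arm sizes under simple randomisation.** The intervention arm follows Binomial(N, 0.5).

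| | N = 140 | N = 60 |
|---|---|---|
| SD of an arm, √N/2 | 5.9 | 3.9 |
| P(exact halves) | 6.7% | 10.3% |
| Central 95% range | 58/82 to 82/58 | 22/38 to 38/22 |
| P(split at least this uneven) | 60/80: 10.8% | 25/35: 24.5% |

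**What unequal arms cost.** Power of the two-sample t-test at d = 0.5:

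- 70/70: 83.6%
- 63/77: 83.2%
- 60/80: 82.8%
- 58/82: 82.5%
- Averaged over all splits of 140: 83.3%
- After 10% loss (126 evaluable): 79.5% at 63/63, against 79.2% averaged over splits

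The loss at the edge of the 95% range is 83.6 − 82.5 = 1.1 points; the expected loss is 0.3 points.

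**Centre balance.** Arm counts within each centre are independent Binomial(m, 0.5). The difference in site share is the proportion of the intervention arm from Florence minus the same proportion in the control arm.

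| Recruitment by centre | P(difference ≥ 10 points) | P(difference ≥ 20 points) |
|---|---|---|
| 70 + 70 | 27% | 2% |
| 90 + 50 | 23% | 1% |
| 30 + 30 | 52% | 16% |
| 40 + 20 | 41% | 12% |

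The chance that at least one centre is split 60:40 or worse is 1 − (1 − 0.120)² = 22% with 70 per centre, and 1 − (1 − 0.362)² = 59% with 30 per centre.

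**What a site imbalance does.** Let D be the site difference in mBI change, in within-site SDs. The shift in the unadjusted contrast is D × (difference in site share). The range D = 0.5 to 0.8 is an assumption.

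- First trial, 10 points: 0.05 to 0.08 SD, against a standard error of √(2/70) = 0.17 SD.
- Pilot, 20 points: 0.10 to 0.16 SD, against √(2/30) = 0.26 SD.

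With equal sites, the share of variance that a centre term removes is (D²/4)/(1 + D²/4), which is 5.9% at D = 0.5 and 13.8% at D = 0.8.

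**The case against.** Several stronger readings are tempting, and the document does not support them.

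- A reader might infer that the stated splits cannot be reached. They can occur by chance. They would also be guaranteed if the word simple is used loosely for a shuffled, fixed-total set of envelopes, which the wording about drawing half the cohort leaves open. The article does not say this. Under one shared series of that kind the arm totals would be exact, but centre balance would not be controlled: the hypergeometric probability of a difference of at least 10 points is 24% at 70 + 70 and 44% at 30 + 30.
- A reader might note that one arm falls below 64 with probability 27.2% (63/77 or worse) and call the trial underpowered. But 64 is not a separate floor for each arm. The effective size per arm is 2·n₁·n₂/(n₁ + n₂), which is 69.3 at 63/77 and 67.9 at 58/82. It drops below 64 only at 49/91 or worse, with probability about 0.05%.
- A reader might infer bias from centre. Simple randomisation is unbiased, and chance centre imbalance is already reflected in the standard error of the unadjusted comparison, so the type I error does not suffer.

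Three further points carry weight. Covariates are commonly left to an analysis plan, which is not shown, so the lack of a centre term is context here and not a fault in itself. The pilot is not sized by power, so lost precision there matters less than it would in a confirmatory trial. And simple randomisation is the least predictable scheme on an unblinded ward. None of this reconciles the method with the exact halves in section 2.5, and an analysis plan cannot restore balance once patients have been allocated.

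**Conclusion.** The point stands as a modest, inexpensive improvement. The named method does not secure the arm sizes stated beside it: they are missed with probability about 93% in ROOMMATE 1st and 90% in a 60-patient pilot. Centre balance is left to chance, with a difference of 10 points or more in 27% and 52% of realisations.

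The comparison remains valid, and the power cost of unequal arms is about one point at most over the likely range. The practical loss is avoidable imprecision and face validity, mainly in the pilot.

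The arm-size probabilities need only 1:1 simple randomisation. The centre figures assume equal recruitment, and they fall to 23% and 41% at 90 + 50 and 40 + 20. The 6% to 14% variance gain rests wholly on the assumed site difference. The conflict over site shares in section 2.3 is a separate inconsistency of wording, and it is the reason the centre split has to be assumed.

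**What to change.** 1. In section 2.5, replace simple randomisation with permuted blocks of random, undisclosed size (for example 4 and 6), stratified by centre, with a separate list for each RCT. This holds the arms at or within a few patients of the stated halves and makes centre shares nearly equal.
2. Include centre as a covariate in the between-arm model.
3. If envelopes for the first RCT are already in use, describe the scheme actually used (independent tosses or a fixed-total set; one series or one per centre), adjust for centre, and use the stratified list for the pilot.
4. In section 2.3, keep either 100 participants per centre or competitive enrolment, and delete the other. Align section 2.5 with the choice.

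The cost is a new list, one line in the analysis and a wording correction; the sample size does not change. The downside is slight predictability at the end of a block on an unblinded ward, limited by keeping block sizes random and undisclosed.
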